## Abstract

**Background:**

The current treatment paradigm for type 2 diabetes mellitus (T2D) typically involves use of multiple medications to lower glucose levels in hope of reducing long-term complications. However, such treatment does not necessarily address the underlying pathophysiology of the disease and very few patients achieve partial, complete, or prolonged remission of T2D after diagnosis. The therapeutic potential of nutrition has been highlighted recently based on results of clinical trials reporting remission of T2D with targeted dietary approaches. During the initial phase of such interventions that restrict carbohydrates and/or induce rapid weight loss, hypoglycemia presents a notable risk to patients. We therefore hypothesized that delivering very low-carbohydrate, low-calorie therapeutic nutrition through community pharmacies would be an innovative strategy to facilitate lowering of glycated hemoglobin (A1C) while safely reducing the use of glucose-lowering medications in T2D.

**Methods:**

A community-based randomized controlled trial that is pragmatic in nature, following a parallel-group design will be conducted (*N* = 200). Participants will have an equal chance of being randomized to either a pharmacist-led, therapeutic carbohydrate restricted (Pharm-TCR) diet or guideline-based treatment as usual (TAU). Pharm-TCR involves a 12-week very low carbohydrate, calorie-restricted commercial diet plan led by pharmacists and lifestyle coaches with pharmacists responsible for managing medications in collaboration with the participants’ family physicians. Main inclusion criteria are diagnosis of T2D, currently treated with glucose-lowering medications, age 30–75 years, and body mass index ≥ 30. The primary outcome is a binary measure of use of glucose-lowering medication. Secondary outcomes include A1C, anthropometrics and clinical blood markers.

**Discussion:**

There are inherent risks involved if patients with T2D who take glucose-lowering medications follow very low carbohydrate diets. This randomized controlled trial aims to determine whether engaging community pharmacists is a safe and effective way to deliver therapeutic carbohydrate restriction and reduce/eliminate the need for glucose-lowering medications in people with T2D.

**Trial registration:**

ClinicalTrials.gov, NCT03181165. Registered on 8 June 2017.

## Background

Diabetes mellitus affects ~ 10% of the Canadian population, with worldwide estimates that 628 million will have diabetes mellitus by 2045 [1]. Approximately 90% of all cases are type 2 diabetes mellitus (T2D) [1]. T2D contributes to a significant increase in morbidity and mortality due to numerous complications attributed to hyperglycemia, hyperinsulinemia, insulin resistance, and associated metabolic dysfunction [2]. The current treatment paradigm for T2D typically involves use of multiple medications to lower glucose levels in hopes of reducing long-term complications [3]. Specifically, if patients with T2D fail to lower hemoglobin A1C (A1C) through lifestyle modification within 3 months, they are started on a treatment regimen beginning with metformin and progressing with the addition of other antihyperglycemic agents until A1C targets are achieved. These antihyperglycemic agents operate through a variety of mechanisms to lower blood glucose; however, the mortality benefits of different add-on medications appear to be different [4–7]. However, this treatment does not necessarily fix the underlying pathophysiology of the disease and studies indicate that T2D is typically a chronic, progressive disease with only < 2% of patients achieving partial, complete, or prolonged remission of diabetes mellitus after diagnosis [8]. When patients are taking multiple medications, the treatment plan requires involvement and integration of care from not only physicians but also pharmacists. Indeed, it has been demonstrated that patients with T2D have more annual visits to their pharmacist than their primary care physician, placing the pharmacist in a key position for overall management of diabetes mellitus [9].

Lifestyle interventions including diet and exercise are often stated as frontline treatments for T2D, either alone or in combination with medications [10, 11]. In particular, the therapeutic potential of nutritional interventions has been highlighted recently based on results of clinical trials reporting “remission” of T2D with targeted dietary approaches [12, 13]. In a non-randomized trial, a remote continuous care model delivering a very low carbohydrate, high fat, non-calorie-restricted diet was effective at lowering A1C, promoting weight loss, and reducing the use of glucose-lowering medications (including insulin) in patients with T2D [14, 15]. The authors reported T2D “reversal” (defined in this study as A1C below diabetes mellitus thresholds and taking no glucose-lowering medications except for metformin) at both 10 weeks [15] and 1 year [14]. In a cluster randomized controlled trial (RCT) involving primary care practices, Lean et al. [12] showed that a calorie-restricted (~ 850 kcal day) total diet replacement method followed by food reintroduction at 12 weeks was effective at inducing remission of T2D (defined as non-diabetic A1C and taking no glucose-lowering medications) in 46% of patients at 1 year. Remission of T2D in this trial was tied to not only weight loss [12] but also rescue of beta-cell function [16]. It is currently unclear whether a very low carbohydrate (< 50 g/day) diet [17] or a more prescriptive low-calorie approach [12] is superior for T2D remission/reversal and we are unaware of any trials specifically comparing these two therapeutic nutrition options. However, it stands to reason that a combined approach incorporating a diet that is both very low carbohydrate and low calorie may be the most potent for lowering blood glucose, promoting weight loss, and achieving T2D reversal.

During the initial phase of therapeutic nutrition interventions that restrict carbohydrates and/or induce rapid weight loss, hypoglycemia presents a notable risk to patients [18, 19]. Indeed, it has been demonstrated that, even prior to weight loss, low carbohydrate diets result in lower glycemia in people with T2D [20]. While rarely addressed in depth, careful medication management and reduction during this period are essential to prevent hypoglycemia and minimize risk [21, 22]. Pharmacists are well-positioned for this role and are educated in medication management and T2D. Studies exploring integrative care wherein pharmacists play an active role in T2D management have demonstrated positive impacts on T2D outcomes [23]. We therefore hypothesized that the innovative strategy of delivering very low carbohydrate, low-calorie therapeutic nutrition through community pharmacies would facilitate lowering of A1C while safely reducing the use of glucose-lowering medications in T2D, particularly in more complex cases in which individuals are taking multiple medications or insulin. To this end, we designed an RCT to determine if community pharmacist-led therapeutic carbohydrate restriction could eliminate glucose-lowering medications and facilitate T2D reversal/remission.

### Study objectives

The study objectives are:
To determine if people with T2D are able to reduce and/or eliminate their need for glucose lowering medications by utilizing a pharmacist-led, therapeutic carbohydrate restricted (Pharm-TCR) diet.To determine if following the Pharm-TCR diet will lead to improvements in body composition, blood glucose control, and cardiometabolic health in people with T2D.To determine if following the Pharm-TCR diet will lead to improvements in quality of life in people with T2D

Data will also be collected for possible future health economics analysis (e.g., medication costs). Trial results will be published.

## Methods/design

A community-based randomized controlled trial that is pragmatic in nature, following a parallel-group design will be conducted. Patients with T2D (*N* = 200) will be recruited from across 12 pharmacy locations in the province of British Columbia, Canada. The pharmacists will use a secure password-protected website maintained by the University of British Columbia (UBC) Centre for Health Evaluation and Outcome Sciences (CHEOS) to implement the random allocation sequence. The secure website provides allocation concealment until the interventions are assigned. The allocation sequence generated was by a researcher from CHEOS using PROC PLAN in SAS 6.4 software. Participants will be stratified by site (pharmacy) and glucose-lowering medications (two or fewer, three or more (or taking exogenous insulin)) and randomized in a 1:1 allocation ratio using permuted block sizes, to either the therapeutic nutrition group or the treatment-as-usual (TAU) group. Due to the nature of the interventions and the involvement required of the pharmacists, they cannot be blinded to final treatment allocations of the participants. The protocol was approved by the University of British Columbia Clinical Research Ethics Board (H16–01539) and the trial was registered on ClinicalTrials.gov (NCT03181165) on 8 June 2017. A flow diagram of the trial is presented in Fig. 1. Additional file 3 contains the SPIRIT 2013 Checklist.

**Fig. 1 Fig1:**
[figure not shown]
Trial Flow Diagram Pharm-TCR, Pharmacist-led, therapeutic carbohydrate restricted diet; TAU, Treatment-as-usual

### Primary outcome

The primary outcome is the proportion of patients with T2D who are either using or no longer using glucose-lowering medications after the 12-week study period.

### Secondary outcomes

The secondary outcomes are:
Hemoglobin A1C (%)Percentage dose reduction in glucose-lowering medications (change in daily dose)Body mass index (BMI) (kilograms/meters squared) and weight reduction (kilograms)Waist circumference (centimeters)Body fat percentage (%)Health-related quality of life (SF-20)Blood lipid profile (total, high-density lipoprotein (HDL) and low-density lipoprotein (LDL) cholesterol, triglycerides), liver function tests (alanine aminotransferase (ALT), aspartate aminotransferase (AST), gamma-glutamyl transpeptidase (GGT)), fasting plasma glucose, pro-insulin, insulin, and C-peptideBlood pressure (millimeters of mercury)Percentage dose reduction in blood pressure-lowering medications (change in daily dose)

### Participant recruitment

We aim to recruit 200 participants (equal probability of randomization to each arm) using a combination of newspaper advertising, online advertising, recruitment posters posted in pharmacies, and by word of mouth in each respective study site location. Potential participants who respond to the recruitment material will be directed to the nearest study site and invited to attend a screening appointment where the study will be fully explained and discussed. Participants will provide written informed consent and their primary care physician will be informed of their participation prior to any data collection. The pharmacists at each site will obtain consent.

#### Inclusion criteria

The inclusion criteria are:
Written informed consentMen and women aged 30–75 yearsDiagnosed with T2D by a physicianUsing at least one glucose-lowering medicationBMI ≥ 30 kg·m^2^

#### Exclusion criteria

The exclusion criteria are:
History of heart attack or coronary artery disease within the previous 2 yearsAny current unstable cardiovascular disorderHistory of liver diseaseHistory of kidney disease or impaired renal functionCurrently pregnant or lactating, or planning on becoming pregnant within the next 12 monthsAny diagnosed neurological disorderHistory of bariatric surgeryHistory of cancer within the previous 5 yearsDietary restrictions that would inhibit adherence to the intervention diet

### Trial procedures

Eligible participants who enroll in the study will undergo baseline assessment of medications and A1C, fasting glucose, triglycerides, liver ALT, AST, GGT, serum triglycerides, HDL and LDL cholesterol, and high sensitivity (hs)-C-reactive protein (hs-CRP). Weight, height, BMI, body fat percentage (measured by bioelectrical impedance), and waist circumference will be taken as anthropometric measurements, and quality of life will be assessed using the SF-20 questionnaire. Participants’ primary care physicians will be notified of all laboratory results as per typical blood requisition (by fax). Participants will fill out a 3-day diet record to assess habitual food intake and the Godin Leisure-Time Exercise Questionnaire to assess typical physical activity. Participants will also be asked to fill out a questionnaire regarding their ethnicity and socioeconomic status. Following the baseline assessments, participants are randomized to either the Pharm-TCR diet group or the TAU control group. A simplified cost-effectiveness analysis including the cost of medications and cost of the foods and pharmacists’ time during the intervention will be conducted as an exploratory outcome.

### Pharm-TCR intervention (0–12 weeks)

Participants randomized to the Pharm-TCR group will meet with a pharmacist and a lifestyle coach at a community pharmacy. The pharmacist will review all medications with the participant and then develop a care plan, including medication recommendations (Additional file 1), to be shared and approved by the participant’s physician (by fax, using existing standard procedures for any medication adjustments recommended by pharmacists). Any adjustments to care made by the physician will be incorporated into the plan. The lifestyle coach or pharmacist will then educate the participant on the components of the intervention and review the Pharm-TCR food options, which are standardized by using a combination of whole foods and supplemental foods from a commercial weight loss diet (Ideal Protein). This commercial diet plan (provided to the participants free of charge) provides a variety of low-carbohydrate, energy-restricted, adequate-protein meals and snacks that are used in combination with a selected group of meats and a wide range of vegetables in order to create a personalized meal plan for each participant. Participants will not otherwise be remunerated for participating in the trial. The macronutrient composition of the meal plan equates to < 50 g of carbohydrates, ~ 35-45 g of fat, and ~ 110-120 g of protein for a total of approximately 850–1100 kcal per day. Pre-packaged foods are used for two meals and one snack each day, with the third meal being prepared from a select group of lower-fat protein sources (e.g., meat, eggs) and low-carbohydrate vegetables. The use of a commercial weight loss diet plan allows for tight control over the amount of carbohydrates consumed and the overall energy intake. This approach was chosen because the consistency makes medication adjustments more predictable and reproducible for the pharmacist. This is essential as the pharmacists will need to manage medication adjustments in anticipation of, and in response to, the rapid glucose-lowering effects of this specific low-carbohydrate low-calorie dietary intervention, even prior to substantial weight loss. For patients who are taking > 30 units of exogenous insulin per day at the start of the study, a modified TCR meal plan is used, which includes 80–100 g of carbohydrates per day. This is to reduce potential risk of hypoglycemia during the insulin de-escalation phase of the study (details below and in Additional file 1). Once a participant’s insulin dose is < 30 units per day they are transitioned to the regular TCR meal plan incorporating < 50 g of carbohydrate per day with remaining insulin dose being reduced by a further 50% on day 1.

Following the initial visit, participants will be required to report to the pharmacy each week to meet with the lifestyle coach and pharmacist in order to monitor progress, collect intervention foods, and receive counseling on dietary adherence for the week ahead (total of 12 visits). At this time, the pharmacist will review the current status of the care plan with the patient, make adjustments as necessary, and communicate as appropriate with their physician. The care plan is individualized to each participant based on their baseline medication usage and blood glucose measurements using a standardized medication deprescribing framework as outlined in Additional file 1. Participants’ medication usage, weight, height, waist circumference, body fat percentage, blood pressure, and capillary ketone levels are also recorded during these visits and a 3-day diet record is filled out again on week 6. On the final visit, participants are assessed for the same blood, anthropometric, quality of life, and habitual physical activity measures that were collected at baseline.

### Treatment-as-usual control (0–12 weeks)

Participants randomized to the TAU group will undergo a medication review by the pharmacist, will be provided with standard medication advice by their pharmacist, and will be given information pamphlets on diet and lifestyle conforming with 2013 Diabetes Canada (formerly the Canadian Diabetes Association) Clinical Practice Guidelines. This information is evidence based and recommends participants to follow a low-fat, low glycemic-index diet and to engage in 150 min of moderate activity per week. Standard clinical practice recommends an A1C test and potential medication adjustments every 3 months (typically an increase in dose or number of glucose-lowering drugs if A1C does not reach below the clinical target of < 7.0%) and therefore the treatment period of 12 weeks was chosen.

Three-day food records will be collected at baseline, week 6, and week 12 to assess the energy and macronutrient content of the foods consumed. Following week 12, TAU participants will return to the pharmacy for a final visit where they are assessed again for all baseline blood, anthropometric, quality of life, and habitual physical activity measures.

In order to help retain TAU-group participants for follow-up testing they will be offered participation in the Pharm-TCR intervention after the TAU period has completed. If a TAU-group participant chooses to try the dietary intervention following completion of the TAU period, the participant is considered to have finished the trial and as such, no study data will be collected from them during this time period.

### Patient safety

During the first 2–4 weeks of the program (when most medication adjustments are made), participants communicate frequently with their pharmacist and lifestyle coach via phone call and/or text messaging and take finger stick blood glucose measurements four times per day (a fasting measurement upon waking, and before lunch, dinner, and bedtime). This allows for feedback and assessment of the medication reductions and helps to reduce any potential risk of hypoglycemia. Participants are instructed on steps to take if blood glucose is < 3.9 mM and/or they have symptoms of hypoglycemia; the steps include consumption of an energy bar containing 15 g of carbohydrates and, if severe or if symptoms do not resolve, reporting to their doctor or emergency room. All observations/results that may pose a risk to health will be discussed with the study team and all adverse events will be recorded. Pharmacists at each site will be closely engaged with participants due to the nature of the intervention. Any safety concerns will be brought to the attention of the study physician, [name] and the lead pharmacist ([name]). A safety committee of two independent physicians with experience in low-carbohydrate diets and T2D will review any adverse events and provide clinical insight into their etiology. These two independent physicians can request stoppage or changes to the ongoing study. The Principal Investigator (PI) ([name]) will meet with [name], [name], and the two independent physicians every 6 months or as often as needed, to review any safety issues or data collection issues. If there are any serious adverse events, the independent physicians or study physician can recommend that any/all participants discontinue participation in the trial. Participants may also choose to discontinue at any time. Pharmacists at each site will have access to the data as they are collected. They will fax or email any data, with no personal identifiers, to the PI or study email address at the UBC. Only study investigators will have access to the faxed or emailed data. Any personally identifying data collected by the pharmacists will be de-identified prior to being sent to the research team.

### Protocol delivery fidelity

A standard training protocol has been developed to minimize variability and maintain the intervention protocol across all pharmacies. Training videos followed by visits in person by the study coordinator will be used to explain the study design, aims, and protocol to the study personnel at each pharmacy. The study coordinator will remain easily accessible to the pharmacy personnel via email and phone throughout the study. The head study pharmacist teaches the medication adjustment framework to the lead pharmacist from each study site, by in-person workshops that include both a lecture portion and multiple case studies. The head study pharmacist will also be available to the site pharmacists via email and phone throughout the study.

### Measurements

The measurements taken at each stage of the study are detailed in the Additional file 2. Height will be measured to the nearest millimeter, using a stadiometer (Seca, model 700, Germany). Body weight will be measured to the nearest 100 g (Tanita, model DC-430 U, IL, USA) with the participant wearing light clothing without shoes. Waist circumference is assessed by measuring the distance around the waist at the top of the iliac crest. Blood pressure will be measured using the PharmaSmart Model PS-2000C (BC, Canada) after the participant has been seated, at rest, with legs uncrossed for at least 5 minutes. Body fat percentage will be assessed by bioelectrical impedance analysis (Tanita, model DC-430 U, IL, USA). Briefly, participants stand on the scale with soles and heels of both of their feet in contact with the electrodes and the participants’ sex, height, and weight are used in combination with the measured resistance to calculate body fat percentage. Tanita has validated this method in people with T2D against dual x-ray absorptiometry (r = 0.89, *p* < 0.0001) [24].

Participants in the Pharm-TCR group will have their capillary ketone levels measured at each weekly visit using a Freestyle Precision Neo device (Abbott Laboratories, CHI, IL, USA). Clinical laboratory requisitions will be given to the participants for blood to be collected at a local clinical laboratory (LifeLabs or Valley Medical Labs) at baseline and post Pharm-TCR intervention or TAU control, to measure A1C, fasting glucose, triglycerides, ALT, AST, GGT, serum triglycerides, HDL and LDL cholesterol, and hs-CRP. A subsample of participants will have fasting C-peptide, insulin, and proinsulin measured to estimate homeostasis model assessment of insulin resistance (HOMA-IR) and beta-cell function based on HOMA-B and C-peptide–proinsulin ratio. This subsample analysis of the plasma samples collected by the clinical laboratory will be performed by the research team at a university laboratory.

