### Statistical analysis

Data will be analyzed on an intention-to-treat basis at the 12-week (post-testing) timepoint. The primary outcome measure is binary - using or not using glucose-lowering medication at 12 weeks - and data will be analyzed by logistic regression, with the stratified allocation factors included as fixed effects together with trial arm and sex. We will derive the odds ratio for use of glucose-lowering medication, and odds will be converted to predicted probabilities (risk differences). Participants who fail to complete the intervention or are lost to follow up from the Pharm-TCR group will be retained in the analyses and will be considered as not achieving the primary outcome. The secondary outcome measures of anthropometrics, blood pressure, medication dose changes, quality of life, and all blood measures will be analyzed using constrained baseline longitudinal data analysis via a linear mixed model [25]. This approach provides a principled method for addressing missing data, including missing baseline data as baseline values are part of the response vector in this model. In addition, study site will be included as a random effect in the linear mixed models to account for site variability in the outcome measures [26]. Model specification will be examined by visual inspection of residuals plots, with appropriate data transformations used if indicated. For the primary endpoint we shall report the odds ratios and predicted probabilities (risk differences) with 95% confidence intervals. Secondary continuous outcomes will be reported as mean differences with 95% confidence intervals. Whenever possible, data analysis will be performed blinded to the allocations.

It is not anticipated that any participants in the TAU group will discontinue glucose-lowering medications; however, to be conservative, the sample size was calculated based on an expected proportion of medication use of 80% in the TAU group and a 20% difference in the proportion of participants on glucose-lowering medications at 12 weeks in the Pharm-TCR group. A sample size of 100 per group provides 80% power to detect a 20% difference in the proportion of patients on glucose-lowering medications, accounting for 20% attrition with a two-sided *P* value of 0.05 (PASS 14 Power Analysis and Sample Size Software, 2015. NCSS, LLC. Kaysville, Utah, USA; ncss.com/software/pass).

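### The single between-arm analysis of fasting insulin, and of any HOMA index built on it, can mistake protocol-driven insulin withdrawal in Pharm-TCR for a physiological change

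*Protocol article*

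**What the plan says.** **What is measured.** Under Measurements, the protocol article states: "A subsample of participants will have fasting C-peptide, insulin, and proinsulin measured to estimate homeostasis model assessment of insulin resistance (HOMA-IR". It adds "beta-cell function based on HOMA-B and C-peptide–proinsulin ratio". The Secondary outcomes section lists insulin, pro-insulin and C-peptide, but not the HOMA indices.

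**How it is analysed.** Under Statistical analysis, "quality of life, and all blood measures will be analyzed using constrained baseline longitudinal data analysis via a linear mixed model", with results reported as mean differences between arms. Study site enters as a random effect, and the Discussion adds sex as a fixed effect. No separate treatment of insulin users is described.

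**Who is in the trial.** One glucose-lowering drug of any kind is enough for entry, and no exclusion criterion names insulin. The Methods/design section stratifies randomisation on "glucose-lowering medications (two or fewer, three or more (or taking exogenous insulin". The intervention section has a separate provision that begins "For patients who are taking > 30 units of exogenous insulin per day at the start of the study".

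**What happens to insulin in each arm.** In Pharm-TCR, the article explains the modified meal plan by saying "This is to reduce potential risk of hypoglycemia during the insulin de-escalation phase of the study", and describes a later step "with remaining insulin dose being reduced by a further 50% on day 1". The treatment-as-usual (TAU) arm has no de-escalation programme. The usual adjustment there is described as "typically an increase in dose or number of glucose-lowering drugs if A1C does not reach below the clinical target", and the sample-size paragraph expects nobody in that arm to stop glucose-lowering medication.

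**The concern.** In someone who injects insulin, a fasting insulin reading can be the sum of the person's own insulin and the drug. The intervention changes the drug directly, and in one arm only. A lower reading at 12 weeks may then show a smaller dose and nothing about insulin resistance or beta-cell function.

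Randomisation does not protect against this, because the dose change comes after randomisation and differs by arm. The constrained baseline does not help either: it sets the arms equal at the start, and the artefact arises afterwards. The medication stratum cannot stand in for insulin use, because it pools insulin users with people on three or more drugs. Even a main-effect adjustment for baseline insulin use would leave an arm-specific shift among users in place.

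At stake is how the mechanistic results are read. A fall in HOMA-IR would be taken as improved insulin resistance, and a fall in HOMA-B as worse beta-cell function. Both could come from the same withdrawal of drug.

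**Working it through.** **The plan's own figure.** The article gives no figure for insulin or HOMA. Its only design figure is for the primary outcome: 100 per group, 80% power, 80% v 60%, 20% attrition, two-sided 0.05. It reproduces: 82 per group with pooled variance, 82/0.8 = 103 after attrition; or 79 unpooled, 79/0.8 = 99. With 80 completers per arm, power is 79.4% (pooled) or 80.7% (unpooled). It has no bearing on this point.

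**Inputs for the artefact.** The article gives none of these for the subsample, so all are assumed ranges:
- f, share of the subsample using exogenous insulin: 10-40%.
- e, share of a user's measured fasting insulin that is injected and detected by the assay: 0-75%.
- r, insulin dose reduction reached by 12 weeks in Pharm-TCR: 50-100%. The article mentions one step of 50%; the total per participant is not given.
- TAU dose unchanged, endogenous insulin unchanged, fasting glucose fixed.
- HOMA-IR proportional to fasting insulin at fixed glucose. The article gives no formula.

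**Formula.** A user's measured insulin after withdrawal, relative to before, is (1 - e) + e(1 - r) = 1 - e·r. A non-user's ratio is 1. Averaging on the log scale over the arm gives

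geometric mean ratio = (1 - e·r)^f.

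On the untransformed scale, if users and non-users start from the same mean, the change is -f·e·r. The same expressions apply to fasting insulin itself, without the HOMA proportionality assumption.

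**Results, with no true change in physiology:**

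| f | e | r | Ratio | Geometric mean | Arithmetic mean |
|---|---|---|---|---|---|
| any | 0 | any | 1.000 | 0% | 0% |
| 10% | 25% | 50% | 0.875^0.1 = 0.987 | -1.3% | -1.25% |
| 20% | 50% | 100% | 0.5^0.2 = 0.871 | -12.9% | -10% |
| 30% | 50% | 100% | 0.5^0.3 = 0.812 | -18.8% | -15% |
| 40% | 75% | 100% | 0.25^0.4 = 0.574 | -42.6% | -30% |

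The direct artefact is zero if there are no users in the subsample (f = 0), if the assay does not detect the injected insulin (e = 0), or if the index is computed from C-peptide. When it is not zero, it favours Pharm-TCR on HOMA-IR. At fixed glucose it goes against Pharm-TCR on HOMA-B.

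**The case against.** A reader might infer that insulin withdrawal will show up as improved insulin resistance. The document does not support that, for these reasons:

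- **Subsample.** The article does not say how it is chosen. Insulin users are eligible for the trial, but nothing says they are in this subsample.
- **HOMA input.** No formula is given, and C-peptide is among the analytes measured to estimate HOMA-IR, so a C-peptide-based index is not ruled out.
- **Assay.** It is not specified, and its detection of injected insulin decides whether there is any direct artefact.
- **Between-arm comparison of HOMA.** This is an inference, since the indices are not listed as secondary outcomes.
- **A safeguard exists.** The C-peptide-proinsulin ratio is already planned and contains no injected insulin.
- **Size.** Any single figure is one point from assumptions. The calculation also holds glucose and endogenous insulin fixed; both would be expected to rise when injected insulin stops, offsetting some of the fall.

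Subsample rules and assay details may properly sit in the full protocol or the analysis plan, so their absence from an article is no error.

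All of this stands, and it makes the point conditional. It does not remove it. Fasting insulin itself is explicitly a secondary outcome, and the article commits all blood measures to one between-arm model. That stated analysis is open to the artefact whenever users are sampled and the assay detects injected insulin. C-peptide is tied explicitly only to the ratio with proinsulin, and measuring it does not change the analysis of insulin.

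**Conclusion.** The concern holds in conditional form. Followed as written, the analysis can produce an arm-differential artefact in fasting insulin, and in HOMA-IR and HOMA-B if insulin is their input. Two conditions are needed for fasting insulin: insulin users in the subsample, and an assay that detects injected insulin. The HOMA indices need the third condition, that insulin rather than C-peptide enters them.

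The size cannot be fixed from the document. Over the assumed ranges it runs from 0% to about -43% in geometric mean HOMA-IR; the far end is the most extreme corner of those ranges and not an expectation. The direction is mixed: favourable to Pharm-TCR on HOMA-IR, unfavourable on HOMA-B.

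This concerns secondary and mechanistic measures. The primary outcome is unaffected, and the artefact does not enter A1C, weight or medication-dose results. The point is worth settling before the insulin results are analysed, because the remedy is cheap and uses data already collected.

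**What to change.** Add to the analysis text that between-arm comparisons of fasting insulin, and of HOMA-IR and HOMA-B where computed from insulin, are restricted to participants not using exogenous insulin at baseline. This is a pre-randomisation criterion applied alike to both arms, and baseline medications are already recorded.

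For the full subsample, report C-peptide-based indices alongside the planned C-peptide-proinsulin ratio. State that C-peptide removes only the direct contribution of injected insulin: injected insulin can suppress endogenous secretion, so withdrawing it in one arm may itself change C-peptide.

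State which analyte enters each HOMA index.

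**Cost.** Analysis wording only, with no change to treatment, sampling or visits. The insulin-based comparisons rest on a smaller subsample. No insulin-based index would be available for insulin users, a group that the Background names as being of particular interest.
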